## Data analysis plan

### Phase 1: Outcome evaluation

Analysis will be undertaken comparing responses between the intervention group and the comparison group using SPSS. As the primary focus in a feasibility study is on the methods for dealing with the feasibility objectives rather than statistical testing [31] results will be presented using descriptive statistics (e.g., mean, proportion) and associated 95% confidence intervals. In addition, to gain further insight into an appropriate sample size for a definitive study, exploratory univariate statistical analyses (e.g., t-tests, chi-squared test) will be performed. At baseline we will compare demographic data and eligibility for bowel screening to determine differences in baseline characteristics between the intervention and comparison groups. This will inform our interpretation of any differences in outcomes and enable us to identify demographic and eligibility differences in those who chose to take up the intervention compared to those who did not. Likert Scale responses to questions assessing knowledge, attitudes and intention to take up screening will be gathered at baseline (both groups), post-intervention (intervention group only) and at 6-month follow-up (both groups). This will enable us to compare understanding of screening between groups at baseline and 6-month follow-up, and, for the intervention group, short-term changes in understanding following the intervention.

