### Sampling approach and recruitment

The population for the study will be individuals attending mosques and Muslim community groups in Luton and Peterborough. We will target mosques that are in catchment areas of GP practices with low bowel cancer screening uptake. The process for identifying potential mosques to participate in the study is outlined in S1 Appendix. Discussions with community leaders will take place to identify which mosques would be best placed to deliver the intervention, and which mosques would be best to support recruitment of participants for the comparison group. Whilst there are limitations to this, and the potential to introduce bias, the intervention is based on the model that the clinicians deliver the intervention within their communities. As a feasibility study, it will also be helpful to work with the mosques and communities who are willing to engage.

Gender specific sessions will be planned in consultation with community leaders, clinicians and patient public involvement representatives to ensure that both men and women are able to participate in the study. As a minimum in both Luton and Peterborough, we plan to work with one mosque for men and one community group for the women in the intervention group plus two mosques/two community groups for the comparison group.

Representatives of those who are eligible for the study are being recruited to ensure that those who rely on family support can participate. Some of those who are eligible may prefer to ask a representative to attend the session rather than attend themselves, due to language or other barriers.

Strategies and approaches to promote the study and to support recruitment of participants for the intervention and comparison groups, will be agreed in consultation with the project advisory group and the patient public involvement (PPI) representatives. These are likely to include 1) information provided at prayer sessions by the Imam (or community group meetings by the group leader); 2) using social media to share links to written information as well as short, pre-recorded video clips in appropriate languages, 3) local radio, 4) printed material in relevant languages, and 5) case studies. We will also engage with key stakeholders e.g. local pharmacists, schools (e.g. family workers), local councillors, women’s groups, and GP practices to raise awareness of the study.

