Clinicians to deliver the intervention will be recruited through the BIMA volunteer network which has over 6,000 members who are professionally vetted and are trained to deliver the presentation and anticipate questions. These professionals are themselves part of the target communities. Individual participants will be recruited through Muslim community/faith groups in the target areas identified, using purposive and opportunistic sampling and recruitment methods, with community leaders and clinicians within the communities promoting the sessions.

Peer-researchers with competence in at least two of the relevant languages (Urdu and Bengali) identified through the mosques will be trained to support the completion of consent forms and study surveys. They will also be trained to support the facilitation of the focus groups. We anticipate that this will avoid the potential situation of lack of trust or openness that may arise if non-Muslim researchers are leading the focus group discussions. Once identified, the research team will hold a virtual training session with the peer-researchers. The training will include an overview of the study, the role of the peer-researchers, with a particular focus on the completion of the consent form and the baseline and post intervention surveys, how to conduct the focus group. Anticipated challenges, and how to overcome them, will also be discussed.

Given the exploratory nature of this study, it was thought that a non-randomised approach would be operationally more practical. Sites will be identified opportunistically, which did not lend itself to randomised design. As this is not a randomised study, participants will be able to choose to be part of the comparison group if they attend a venue which is acting as an intervention site and prefer not to access the intervention, and participants who attend a venue which is acting as a comparison group site will be able to complete the intervention if they wish to receive the intervention. Data analysis will be carried out on individual responses. Given the planned sample size it will be difficult to investigate outcomes by ethnic group within the Muslim population.

To encourage participation in both the intervention and the study groups in this study, we propose to make a monetary donation of five hundred pounds to each participating mosque. Given the limited study budget it will not be possible to provide individual incentives.

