One intervention session will be delivered at each intervention site as part of the feasibility study. Part of the feasibility study will be to assess how many participants attend the session as a result of the promotion as outlined above.

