## Evaluation data collection and protocol

### Phase 1: Outcome evaluation

#### Participant surveys

Participants in the intervention and comparison groups will provide data through self-completed surveys. The survey tools included as supporting information in S2–S4 Appendices. Participant information sheets will be translated into Bengali and Urdu and will be provided to participants in the intervention and comparison groups ahead of asking them to participate. Printed copies will be made available at the participating mosques. These will be available in digital and hard copy.

Where possible, participants will be asked to complete the consent and survey forms digitally, shared via text message or email. This is to reduce the administrative burden of data entry given the limited study resources. A digital consent form will be included at the start of the baseline survey to gain participant consent. Feedback from stakeholders suggested that we host ‘drop-in’ sessions where peer-researchers are available to support participants with survey completion. We will explore this and plan accordingly with the participating venues for each of the three surveys.

Participants in the intervention and comparison groups will be asked to complete a baseline survey. A survey used in a previous study [32] has been adapted to suit the current study. Participants receiving the intervention will need to complete this before attending the information session (either face-to-face or virtually). For those attending the information sessions face-to-face, and who have not yet completed the consent and baseline survey online, paper forms will be available. Peer-researchers will be available to support participants to complete the survey. If individuals do not fill in the baseline survey, they will not be included as participants, but they will still be permitted to attend the information sessions.

Participants in the control group will be provided with the link to the online consent and baseline survey forms. This information will be available at the participating control sites for participants to request, or they will be able to sign up to participate and the link will be sent to them by text message or email. ‘Drop in’ sessions to support with survey completion at control sites will also be explored.

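### The baseline contrast between groups mixes venue with individual choice, so it cannot be read as showing who takes up the session and who does not

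*Protocol article*

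**What the plan says.** The protocol article (Data analysis plan, Phase 1: Outcome evaluation) compares demographic data and screening eligibility at baseline to "determine differences in baseline characteristics between the intervention and comparison groups". It gives two uses for this table. One is to help interpret any differences in outcomes. The other is to "identify demographic and eligibility differences in those who chose to take up the intervention compared to those who did not".

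How people come to be in each group is set out elsewhere:

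- Sampling approach and recruitment, on who decides a venue's role: "Discussions with community leaders will take place to identify which mosques would be best placed to deliver the intervention", and likewise "which mosques would be best to support recruitment of participants for the comparison group".
- The same section, on the minimum plan for each town: one mosque for men and "one community group for the women in the intervention group plus two mosques/two community groups for the comparison group".
- The same section, on delivery: "One intervention session will be delivered at each intervention site as part of the feasibility study". No session is described at comparison sites.
- Participant surveys, on how comparison participants get the consent and baseline links: "This information will be available at the participating control sites for participants to request", or they can sign up and be sent the link.
- Sampling approach and recruitment, on preference: people may "choose to be part of the comparison group if they attend a venue which is acting as an intervention site" and would rather not have the session. People at comparison venues may have the session if they want it.
- The intervention: a recorded or live online version is offered as an alternative.

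**The concern.** The second use treats everyone in the comparison group as a person who did not choose the session. Someone who enrols through a control site has not, on the text, been offered a session at their own venue and declined it. They may be in the comparison group because of where they worship or meet.

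Venues are chosen for their role, not randomised, so their congregations may differ in age, language, deprivation or screening eligibility. Reported under the plan's wording, such differences would be presented as characteristics of people who accept or decline the session. A real difference between acceptors and decliners could also be diluted. Who comes forward bears on accessibility and on how a wider roll-out would be targeted, so a misattributed difference could mislead.

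**Working it through.** **The plan's own figures.** The article plans 100 intervention and 150 comparison participants and states precision of ±0.1 and ±0.08 for a proportion. The 95% half-width at p = 0.5 is 1.96 × √(0.25/n), which gives 0.098 for n = 100 and 0.080 for n = 150. Both figures reproduce. The point concerns what the contrast means and disputes no stated number.

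**What the contrast estimates.** Let

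- s = share of the comparison group who declined at an intervention venue (not given in the article);
- C = true difference between takers and decliners within a venue, in percentage points;
- V = difference between intervention and comparison venues, in percentage points;
- d = share of comparison-site participants who would have declined if offered the session at their own venue (not given).

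For simplicity, people from comparison sites who take the session are left out. Then

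observed contrast = s × C + (1 − s) × (V + d × C).

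The plan reads the left-hand side as C. That is right only if s is close to 1, or if V is zero and d is close to 1.

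**Illustration with assumed values.** Each true difference is set to 15 points in turn, and the other to zero.

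| s | V = 15, C = 0 | C = 15, V = 0, d = 0 | C = 15, V = 0, d = 0.3 |
|---|---|---|---|
| 0 | 15.0 | 0 | 4.5 |
| 0.10 | 13.5 | 1.5 | 5.55 |
| 0.25 | 11.25 | 3.75 | 7.125 |
| 0.50 | 7.5 | 7.5 | 9.75 |
| 1 | 0 | 15 | 15 |

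Worked row, s = 0.10 (15 of 150 people):

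- venue only: 0.90 × 15 = 13.5;
- choice only, d = 0: 0.10 × 15 = 1.5;
- choice only, d = 0.3: 15 × (0.10 + 0.90 × 0.3) = 5.55;
- choice only, d = 0.5: 15 × (0.10 + 0.90 × 0.5) = 8.25.

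Two things follow. With small s, a difference that is wholly due to venue passes largely intact into what the plan would call choice. A difference wholly due to choice shrinks, by an amount that depends strongly on d. At s = 0.50 and d = 0, a contrast of 7.5 points arises equally from venue alone or from choice alone, so the contrast itself cannot tell the two apart.

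**Precision of a within-venue comparison.** With an assumed 15 decliners, the half-width for a proportion is 1.96 × √(0.25/15) = 0.253, or about ±0.25.

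**The case against.** A reader might infer that the contrast shows venue and nothing of choice. The documents do not support that. Switching by preference is allowed at both kinds of venue, and virtual access adds another route, so choice is part of the contrast. It just cannot be separated from venue.

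A reader might also infer that most comparison participants come from other venues, or that a choice difference must shrink to a point or two. Planning separate comparison venues makes the first plausible, but the article gives no count. The second holds only if comparison-site participants resemble takers (d = 0). If many of them would have declined, the dilution is milder, as the last column of the table shows.

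There is also a fair case that little turns on this. The primary outcomes, acceptability and accessibility, are assessed through focus groups and interviews. Turnout at sessions is a separate feasibility question. The first use of the baseline table, to help interpret outcome differences, is sound and unaffected. The article already admits that venue selection may introduce bias. A within-venue breakdown may exist in a fuller plan that is not shown, and the survey forms, also not shown, may already record the venue.

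All of this limits the weight of the point without removing it. The article does more than leave a detail open: it states what a named contrast will show, and its own recruitment plan does not bear that out. The admission of bias in the recruitment section is not carried through to this sentence.

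**Conclusion.** The stated inference does not follow. Group membership depends on venue role as well as on preference, so the baseline contrast confounds the two and cannot be read as a description of who accepts or declines the session.

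The size of the distortion is unknown. It depends on the share of comparison participants from each kind of venue and on how many comparison-site participants would have declined, and the documents give neither. The figures above rest on assumed shares and assumed 15-point differences. What does not rest on particular values is that the contrast cannot isolate choice unless nearly all comparison participants are decliners from intervention venues, or venues are alike and nearly all comparison-site participants would have declined too. This is a matter of interpretation that should be corrected. It does not undermine the study.

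**What to change.** In the Phase 1 data analysis plan:

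1. Describe the full intervention-versus-comparison baseline table only as group differences that mix venue and preference. Keep its use in interpreting outcomes.
2. Compare those who took up the session with those who did not among people enrolled at intervention venues only, and present the result descriptively.
3. List separately any comparison-site participants who took the intervention.
4. Hold enrolment venue and receipt of the session as two separate variables.

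The cost is a reworded sentence and, if venue is not already recorded, one more variable. No extra recruitment is needed. The downside is that the decliner group will be small. It will also be selective: people who do not complete the baseline survey are not participants, so the only decliners seen are those who turned down the session but still consented and filled in the survey. The result can describe that group but should not be generalised to everyone who stays away.

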### Phase 2: Process evaluation

Focus groups will be digitally recorded and shared securely (by encrypted file) with the service commissioned to complete the transcription. Once transcribed, that data will be returned securely, and the recordings will be deleted by the transcription service. A data sharing agreement is in place between the University of Hertfordshire and the transcription service. Remote interviews will be recorded via Zoom or MS Teams. Recordings will be shared with the transcription service as for the focus group data. Data will be stored securely on University of Hertfordshire and NHS systems. Information will be shared via secure platforms or encrypted in line with information governance requirements.

Interviews and focus groups will be transcribed verbatim, uploaded to NVivo software and subject to a General Inductive Approach (GIA) analysis [34]. Fieldnotes will also be uploaded as part of the data set and subject entered into NVivo for analysis. The analytical aim will be to identify and explore links between contexts (C), mechanisms (M) and outcomes (O). Data will be coded into COM dyads and developed into a framework to generate mid-range theories around processes and context [35]. Particular attention will be paid to discordant voices. The research team will meet regularly to achieve consensus in data interpretation.

## Patient and public involvement

The project will take a collaborative approach, which values co-production with partners in the region. Clinicians from the British Islamic Medical Association (BIMA) who are also part of the Muslim community, and who are Muslim themselves, have been and will continue to be involved in designing, planning and delivering the project.

Members of the Public Involvement in Research Group (PIRG) at the University of Hertfordshire, who are also Muslims, commented on an initial project proposal. The PIRG will continue to be involved throughout and offer feedback and critical guidance on the project including ethics, recruitment and dissemination.

Community leaders will also be involved and consulted throughout the project to ensure that they meet the needs of their communities.

The project has been discussed at the NHS England Bowel Cancer Screening Inequalities Forum. It has also been discussed at a local Cancer Survivor Patient Forum to get their views.

There are two patient and public involvement representatives on the advisory group. They are consulted on different aspects of the project. Examples include 1] planned approaches to ensuring that women can participate in the project 2] use of appropriate language in participant information and consent forms and survey questions (not too technical, translated if possible).

## Ethics

### Approvals

University of Hertfordshire are the study sponsors and have reviewed and approved the study protocol and the ethics application, protocol number HSK/SF/NHS/02971.

Ethical approval was sought through the Integrated Research Application System ((IRAS)). The Health Research Authority ((HRA)) confirmed that full HRA approval was not required as it did not involve NHS sites. As the study does involve a sensitive topic and there is an element of burden to the participants, the study required a Research Ethics Committee review ((rather than a proportionate review)). The project team met with the Cambridge Central Research Ethics Committee ((REC)) on the 8 October 2021. The REC required minor changes to the protocol and the participant information sheet to include detail on how any safeguarding issues identified would be managed. The study documents were revised accordingly. Ethical approval was granted on the 27 October 2021, REC reference number 21/EE/0231.

### Participant information and consent

Participant information (translated into one or two additional languages) and a consent form will be available prior to participation in the study for those in the intervention and the comparison groups as well as the clinicians recruited to deliver the intervention. If required, we will also allow for verbal consent to be obtained at face-to-face intervention sessions (agreed in the ethical approval), as Patient and Public Involvement representatives indicate that participants may be reluctant to provide a signature or written consent.

Participants will be able to withdraw from the study at any time.

The UK Policy Framework for Health and Social Care Research will guide the approach to confidentiality aspects of this study [36].

Participants will be asked to provide patient identifiable information to validate objective data on actual screening uptake. Only researchers who require specific participant information will be given access.

Responses and participation will remain anonymous in any published materials relating to the study.

### Safeguarding and support

If information disclosed by participants (through surveys, the intervention session, or the focus groups) raises any safeguarding concerns, a member of the project team will contact the individual to discuss this with them, as outlined in the consent form. We will aim to get their consent to refer them to an appropriate individual or organisation who may be able to provide support. Depending on the nature of the concern, this may be the Imam, the clinician delivering the intervention session, or the individual’s GP. If more serious in nature, the safeguarding policies and procedures of the leading organisations (University of Hertfordshire and NHSE England and Improvement) will be followed. It may also be appropriate to refer to the safeguarding policies of the participating mosques/ community groups.

Individuals who have been affected by cancer, directly or indirectly, may find some of the questions in the survey, or information in the intervention session upsetting or difficult. Details of individuals and organisations who may be able to offer support have been included in the participant information sheet. This includes the clinician delivering the intervention session; the Imam or community leader in their role of providing pastoral support; or the individual’s GP. Details of cancer charities have also been included:

Bowel Cancer UK: visit www.bowelcanceruk.org.ukCancer Research UK: visit www.cancerresearchuk.org or call 0808 800 4040Macmillan Cancer Support: visit www.macmillan.org.uk or call [name]

The surveys, participant information sheet and consent form have had input from patient and public involvement representatives to ensure that they are appropriate and culturally sensitive.

The clinicians delivering the intervention will also ensure that the information is delivered in a culturally sensitive way. Clinicians are trained and experienced in talking to patients about health and care issues.

